## Abstract

**Background:**

Many Canadian adolescents and young adults with mental health problems face delayed detection, long waiting lists, poorly accessible services, care of inconsistent quality and abrupt or absent inter-service transitions. To address these issues, ACCESS Open Minds, a multi-stakeholder network, is implementing and systematically evaluating a transformation of mental health services for youth aged 11 to 25 at 14 sites across Canada. The transformation plan has five key foci: early identification, rapid access, appropriate care, the elimination of age-based transitions between services, and the engagement of youth and families.

**Methods:**

The ACCESS Open Minds Research Protocol has multiple components including a minimum evaluation protocol and a stepped-wedge cluster randomized trial, that are detailed in this paper. Additional components include qualitative methods and cost-effectiveness analyses. The services transformation is being evaluated at *all* sites via a minimum evaluation protocol. Six sites are participating in the stepped-wedge trial whereby the intervention (a service transformation along the key foci) was rolled out in three waves, each commencing six months apart. Two sites, one high-population and one low-population, were randomly assigned to each of the three waves, i.e., randomization was stratified by population size. Our primary hypotheses pertain to increased referral numbers, and reduced wait times to initial assessment and to the commencement of appropriate care. Secondary hypotheses pertain to simplified pathways to care; improved clinical, functional and subjective outcomes; and increased satisfaction among youth and families. Quantitative measures addressing these hypotheses are being used to determine the effectiveness of the intervention.

**Discussion:**

Data from our overall research strategy will help test the effectiveness of the ACCESS Open Minds transformation, refine it further, and inform its scale-up. The process by which our research strategy was developed has implications for the practice of research itself in that it highlights the need to actively engage all stakeholder groups and address unique considerations in designing evaluations of complex healthcare interventions in multiple, diverse contexts. Our approach will generate both concrete evidence and nuanced insights, including about the challenges of conducting research in real-world settings. More such innovative approaches are needed to advance youth mental health services research.

**Trial registration number:**

Clinicaltrials.gov, ISRCTN23349893 (Retrospectively registered: 16/02/2017).

**Electronic supplementary material:**

The online version of this article (10.1186/s12888-019-2232-2) contains supplementary material, which is available to authorized users.

## Background

Mental disorders usually begin before the age of 25 [1] and can persist [2], sometimes in changing forms [3]. They often disrupt the pursuit of the typical social and educational developmental milestones of youth and impose much suffering and societal cost [2, 4, 5]. Mental illness is the leading contributor to disability-adjusted life years among people aged 0–24 years in high-income countries [6]. In Canada, suicide accounts for 20–25% of deaths among 15- to 24-year-olds [7]. Canada’s Indigenous youth suffer exceptionally high rates of mental health problems, substance abuse, and suicide [8, 9].

Adolescence and young adulthood represent a critical window for early detection and intervention because that is when most mental illnesses arise [1] and are presumably most amenable to treatments that can improve long-term outcomes and reduce disease burden [10, 11]. Moreover, longer durations of untreated mental illnesses are generally associated with worse clinical and functional outcomes and greater personal and familial suffering [12–14]. Yet, many youth with mental health problems remain untreated or face delayed detection [15].

In Canada, where 18.5% of youth aged 15 to 24 are affected by mental and substance use disorders [16], a 2012 survey found that only 49.7% of youth with mental health problems and 25.8% of those with substance use disorders had sought professional help in the preceding year [17]. Our systematic review [18] found that help-seeking youth’s pathways to mental healthcare were often complex, stressful/negative (e.g., involving emergency rooms or police) and delay-prone. Across much of Canada, long waiting lists significantly delay evaluation and treatment [19] and youth are also excluded from care based on not meeting specific diagnostic criteria [20]. Canadian youth mental healthcare is also marred by improper transitions between child-adolescent and adult services; a paucity of evidence-informed interventions; fragmented, inefficient and siloed system components [21, 22]; and little involvement of patients and their families in service design and planning, despite growing acknowledgement of the value of such involvement [23–26]. Consequently, services fail to engage and meet the needs of youth and their families.

Addressing these issues is the remit of ACCESS Open Minds, a research network established under the Strategy for Patient-Oriented Research (SPOR) [24] of the Canadian Institutes of Health Research (CIHR). This five-year project draws on the experiences of Australian, Irish and British youth mental healthcare improvement initiatives and previous work on early intervention in psychosis [27–29] Partnering with multiple stakeholder groups (youth and families with lived experience, service providers, researchers, and decision-makers), ACCESS Open Minds developed, and is implementing and evaluating a transformation of services for youth (aged 11 to 25) with all types and severities of mental health difficulties at 14 sites across Canada [30].

ACCESS Open Minds is implementing strategies to increase youth referrals and help-seeking; accelerate response times; provide timely access to appropriate interventions as per established benchmarks; eliminate age-based transitions between services; and engage youth and families. The transformation also involves creating youth-friendly, stigma-reducing, community-based spaces that allow walk-in access to integrated services and supports. It is hypothesized that this transformation will improve the reach, timeliness, appropriateness, quality, acceptability, clinical and functional outcomes, and subjective experience of mental health services. The ultimate goal is to create a sustainable and scalable model for timelier, friendlier, and more effective youth mental healthcare.

### Objectives

This study evaluates the effectiveness of the ACCESS Open Minds model using a multi-method design that includes a minimum evaluation protocol, a pragmatic stepped-wedge randomized trial, a qualitative strategy, and a cost-effectiveness evaluation. This paper focuses on the minimum evaluation protocol and the stepped-wedge trial. The qualitative and economic evaluations will be described in separate publications.

Given the breadth of issues addressed, strategies deployed and populations targeted, we ask the following main questions in this study:
How and to what extent does ACCESS Open Minds work to identify youth in need and improve their access to high-quality mental healthcare?Among which youth groups and in which contexts is the transformation most and least beneficial?

These research questions are operationalized through well-defined primary and secondary objectives and related hypotheses.

### Primary objectives

To determine if the ACCESS Open Minds model:
Increases early case identificationHypothesis 1: There will be a significant increase in the number of youth seeking help at, or being referred to, study sites over the course of the project.Reduces systemic delay in responding to referrals/help-seekingHypothesis 2: The proportion of youth being offered an initial assessment by a trained clinician within 72 h of referral/help-seeking will increase and be sustained at or above benchmark levels (once attained) over the course of the project.Reduces treatment delay (i.e., the delay between the initial evaluation and the commencement of appropriate treatment)Hypothesis 3: Over the course of the project, a higher proportion of youth seeking services at sites will be offered appropriate care/interventions within 30 days (the Canadian Psychiatric Association’s benchmark) [31]. For urgent cases, the guidelines recommend commencing treatment in less than 30 days. This will be examined separately for youth with and without serious mental illnesses.

### Secondary objectives

To determine if the ACCESS Open Minds model:
4.Simplifies pathways to mental healthcareHypothesis 4: Over the course of the project, youth will make fewer help-seeking contacts in the previous 12 months before accessing services at project sites.5.Improves outcomes for youth served at project sitesHypothesis 5: The clinical, social-vocational and subjective functioning of youth will significantly improve over the course of their follow-up. An additional objective is to determine which outcome domains are most impacted by treatment. The lengths of follow-up will vary depending on youth’s needs, severity of illness, etc.6.Satisfies youth and their familiesHypothesis 6: At least 75% of service users and their families/carers will be satisfied with services and service providers at all completion time-points.

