CCHS-MH 2012 questions related to services sought and received	Clinician-interview with youth and/or family/carer, plus any available records	Number of help-seeking contacts made for problems with mental health/substance use and whether or not services were received in previous 12 months (Hyp. 4)	None; can examine type of contacts (formal, informal, etc.)	Intake
*Clinical improvements*				
Kessler-10 Psychological Distress Scale (K-10)	Youth	Unidimensional factor of distress as being linked to mental ill-health and varied diagnoses (Hyp. 5)	Cut-offs based on overall score (e.g., mild distress)	Intake, Months 1, 3, 6, 9, and 12
Clinical Global Impression of Severity (CGI)^x^	Clinician	Clinician’s rating of severity of youth’s presenting problem over time (Hyp. 5)	None	Intake, Months 1, 3, 6, 9, 12 and 24/end of services
Self-rated health and self-rated mental health (SRH-MH)	Youth	Self-assessment of health and mental health, each on a single 5-item Likert scale (Hyp. 5)	None	Intake, Months 1, 3, 6, 9, and 12
*Functional improvements*				
Social and Occupational Functioning Assessment Scale (SOFAS)^x^	Clinician	Social and vocational functioning on a 0 to 100 scale (Hyp. 5)	None	Intake, Months 1, 3, 6, 9, 12 and 24/end of services
*Subjective/Well-being improvements*				
Goals tool inspired by the Goals-based Outcome (GBO) tool*^x^	Youth	Self-rated progress on 3 chosen goals (Hyp. 5)	None	Intake, Months 3, 6, 12 and 24/end of services
Outcome Rating Scale (ORS)^x^	Youth	Overall outcome/ functioning/ well-being (Hyp. 5)	None; Items related to overall; individual; interpersonal; and social outcomes can be examined separately	Intake, Months 6, 12 and 24/end of services
World Health Organisation Quality of Life – Brief (WHOQOL)*	Youth	Self-assessment of quality of life (Hyp.5)	Four domains: physical health, psychological health, social relationships, and environment	Intake, Months 6, 12 and 24/end of services
*Service experiences*				
OPOC^x^	Youth, family	Satisfaction (Hyp. 6)	Access to service, services provided, participation/ rights, therapists/support workers/staff, environment, discharge, recovery outcome, service quality	Months 1, 3, 6, 9, 12 and 24/end of services
Session Rating Scale (SRS)^x^	Youth	Working Alliance (Hyp. 6)	None; Items related to relationship; goals or topic; approach or method; and overall can be examined separately	Intake, Months 6, 12 and 24/end of services

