Given the larger goal of evaluating impacts for all youth across settings, most measures in our protocol are nomothetic. However, being a patient-oriented research project, it was thought important to include an idiographic measure inspired by the Goals Based Outcome (GBO) [74]. It allows youth to rate their progress toward three self-identified, personally salient goals during their follow-up. Family members/carers are also invited to choose and rate progress towards three goals in relation to their loved ones’ services. Pooled data on goal attainment will help evaluate the effectiveness of services, as has been done in the United Kingdom with the GBO [75–77].

*Service experiences*: To assess the extent to which ACCESS Open Minds transforms cultures of care, the youth and family versions of the Ontario Perceptions of Care (OPOC) [78] (a validated tool developed in Canada) will be used to assess satisfaction with the accessibility, quality and other aspects of services. Therapeutic alliance will be assessed using the Session Rating Scale (SRS) and youth’s perceptions of empowerment and engagement using the Youth Efficacy/Empowerment Scale [79]. These tools complementarily assess alliance with individual care providers (SRS) [80] and overall satisfaction with a service (OPOC).

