### Statistical plan

Every attempt will be made to collect outcome data from all participants, including those who do not complete treatment. Youth will be considered as having a serious mental illness if they attain the relevant scale-specific cut-off scores on the K-10, SOFAS and/or the CGI-severity scale.

*Pre-post minimum evaluation protocol*: For each site, general linear models with repeated measures will be used to analyze differences over time per site (for hypotheses pertaining to increased referrals, evaluations within 72 h, treatment within 30 days, number of prior help-seeking contacts, and satisfaction with services) and per youth (at baseline and at follow-up timepoints for the hypothesis pertaining to improvements in functioning). Generalized estimation equations will be employed for parameter estimation. Respective baseline values will be added to the model as a covariate. Additional analyses will include examining hypothesis 3 separately for youth with and without serious mental illnesses, examining inter-site heterogeneity, and identifying baseline predictors of response to treatment. Finally, outcomes will be examined separately for large urban, small urban/rural and Indigenous contexts.

*Trial*: Youth demographics and clinical data will be described using means and standard deviations and trial waves will be compared using t-tests or non-parametric tests for quantitative characteristics. The effect of the interventions on the three primary and all secondary outcomes will be quantified using mixed or multi-level models to integrate cluster/wave and time effect. The unidirectional crossover design of the stepped-wedge trial allows us to test the effect of the intervention at both within- and between-cluster levels. Mixed models allow stratification (e.g., by population sizes); inclusion of missing data with the principle of intention to treat; and adjustment for baseline differences.

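### Hypothesis 6 sets a fixed 75% satisfaction benchmark, but neither analysis the article describes for satisfaction compares it with 75%, and the OPOC has no youth-level baseline for the stated covariate

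*Protocol article*

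**What the plan says.** Under Secondary objectives, Hypothesis 6 reads: "At least 75% of service users and their families/carers will be satisfied with services and service providers at all completion time-points". The Methods paragraph of the abstract describes the same hypothesis as one of greater satisfaction among youth and families.

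The Statistical plan, in its paragraph on the pre-post minimum evaluation protocol, says that "general linear models with repeated measures will be used to analyze differences over time per site", and lists what this covers: "for hypotheses pertaining to increased referrals, evaluations within 72 h, treatment within 30 days, number of prior help-seeking contacts, and satisfaction with services". It then adds, with no exception: "Respective baseline values will be added to the model as a covariate". The trial paragraph says that the effect of the intervention on the primary and all secondary outcomes will be estimated with mixed or multi-level models.

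Table 2 lists the OPOC (youth and family versions) as the satisfaction measure for Hypothesis 6, given at "Months 1, 3, 6, 9, 12 and 24/end of services". The Session Rating Scale (SRS) is also tagged to Hypothesis 6. Its construct is working alliance, and its schedule does include Intake. The Outcome measures section separates the two: "These tools complementarily assess alliance with individual care providers (SRS) [80] and overall satisfaction with a service (OPOC)".

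Hypothesis 2, a primary hypothesis, has a level component too. The proportion offered an assessment within 72 h is to increase and then "be sustained at or above benchmark levels (once attained)". The article gives no numerical value for that benchmark proportion.

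**The concern.** A claim about a level and a claim about change are different questions. Hypothesis 6 as worded is true or false according to where satisfaction stands against 75% at each time-point. A model of differences over time, or of control against intervention periods, estimates whether satisfaction moved. Its result can be strong when the benchmark is missed and null when the benchmark is comfortably met. If the report gives only the analyses described, readers get an answer that does not bear on the hypothesis as stated under Secondary objectives.

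The covariate sentence adds a practical problem. Youth have not yet rated the service on the OPOC at Intake, so the model cannot be fitted to the OPOC with each youth's own baseline.

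**Working it through.** **1. The plan's own figures.** No sample size, power, alpha or cut-point is given for Hypothesis 6. The only computed size is the projected 3616 participants. It reproduces: 0.60 × 6029 = 3617.4, and Table 1 with its footnote gives 3403 + 213 = 3616. It does not bear on the 75% benchmark.

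**2. Wording against analysis.**

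| Place | Question addressed | Compared with 75%? |
|---|---|---|
| Abstract, Methods | Does satisfaction increase? | No |
| Secondary objectives, Hypothesis 6 | Is at least 75% satisfied at every time-point? | Yes |
| Statistical plan, pre-post | Differences over time per site, baseline-adjusted | No |
| Statistical plan, trial | Effect of the intervention | No |

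The two analyses match the abstract. Neither matches Hypothesis 6.

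**3. How the answers can diverge.** Assume 300 independent respondents in each of two periods (an assumption; clustering ignored) and a two-sided 5% test. For a rise from 60% to 72%:
- pooled standard error = √(2 × 0.66 × 0.34 / 300) = 0.0387
- unpooled standard error = √((0.60 × 0.40 + 0.72 × 0.28) / 300) = 0.0384
- power = Φ((0.12 − 1.96 × 0.0387) / 0.0384) = Φ(1.15) ≈ 88%

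Both values are below 75%, so the change is very likely to be declared while the hypothesis fails. At a constant true 85%, the chance that an observed proportion among 300 reaches 75% is above 99.9%, yet there is no change for the model to find.

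**4. Baseline.** The OPOC schedule starts at Month 1, so a youth-level Intake value does not exist. A site-level starting value could exist: the pre-post model is per site, Study design plans pre-post comparisons at some sites, and trial clusters contribute control-period observations. The article does not say that this is what baseline means for satisfaction. The eligibility section restricts the study of outcomes to youth receiving transformed services, which makes a pre-transformation value uncertain.

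**5. Precision of a direct estimate.** Assumptions: 500 respondents at a time-point, 12 sites (Limitations says two of the 14 could not follow the protocol), ICC 0.02 to 0.05, true proportion 75%. Half-width = 1.96 × √(0.75 × 0.25 × DE / 500).
- Equal sites: DE = 1 + (500/12 − 1) × ICC = 1.81 or 3.03, so the half-width is 5.1 or 6.6 points.
- Unequal sites: the Table 1 targets and footnote minima for the 12 sites (277, 864, 93, 236, 700, 329, 39, 865, 68, 56, 44, 17; total 3588, mean 299) have CV² ≈ 1.09. DE = 1 + ((1 + 1.09) × 500/12 − 1) × ICC = 2.7 or 5.3, so the half-width is 6.3 or 8.7 points.
- With t on 11 degrees of freedom (2.20) in place of 1.96, the unequal-site figures become 7.0 and 9.8 points.

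**6. Why the decision rule must be fixed.** Take four Table 1 site targets as illustrative respondent numbers, a true 80% (which meets Hypothesis 6), and independent observations.

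| n | Exact one-sided 0.025 test of 75%, one time-point: power | Observed at least 75% at all six time-points: chance |
|---|---|---|
| 39 | 9% | 19% |
| 93 | 14% | 52% |
| 236 | 40% | 86% |
| 864 | 93% | 99.9% |

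The two rules give very different chances of supporting a hypothesis that is true.

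**The case against.** The strongest reply is that the change model has a purpose. The abstract frames satisfaction as something expected to increase, and the model answers that. The Statistical plan also nowhere says that Hypothesis 6 stands or falls on a significant time effect. The percentage satisfied could simply be tabulated, a repeated-measures model can yield time-point estimates, and an unseen analysis plan may set out the comparison. This stands to the extent that a reader should not infer that Hypothesis 6 will never be tested. What the article supports is narrower: no analysis it describes makes the comparison with 75%, and the analysis it does name for satisfaction addresses something else.

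A reader might also infer that no baseline exists for satisfaction at all. The documents do not support that. In the per-site group, baseline can be read as a site's starting value. Referral counts sit in the same group and cannot have a youth-level Intake value. The SRS, also tagged to Hypothesis 6, is rated at Intake. Only the youth-level OPOC baseline is shown to be absent.

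On Hypothesis 2, a reader might infer that the planned model cannot show that a level was sustained. That goes too far: the model addresses the increase directly, and period estimates from it could show the rest. What is missing is the benchmark proportion to set them against.

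Finally, requiring the lower confidence bound to reach 75% is stricter than Hypothesis 6 states. That objection is sound, and the rule should be the sponsor's explicit choice.

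**Conclusion.** The mismatch holds and is visible in the article itself. Hypothesis 6 is an absolute benchmark, the abstract words it as an increase, and both analyses described for satisfaction estimate change or an intervention effect. Following the text as written would not answer Hypothesis 6 as worded. The youth-level baseline covariate cannot be fitted for the OPOC, and a site-level alternative is possible but unstated.

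This conclusion rests on the wording alone. The size of any interval does not: about 5 to 7 points for equal sites and about 6 to 9 points for Table 1's unequal sites, under the assumed 500 respondents, 12 sites and ICC of 0.02 to 0.05. The point concerns a secondary hypothesis; the Hypothesis 2 part is a smaller clarification.

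**What to change.** - Reconcile the abstract with Hypothesis 6, stating whether the claim is a level, an increase, or both.
- As the analysis of Hypothesis 6, estimate the proportion satisfied on the OPOC at each time-point, separately for youth and families. Use a confidence interval that allows for clustering in few and unequal sites, and compare it with 75%.
- Fix in advance the OPOC cut-point for being satisfied, and whether the point estimate or the lower confidence bound must reach 75%.
- Exempt the OPOC from the baseline covariate, or define its baseline at site level and say which period supplies it.
- Keep the change model as a supplementary analysis that serves the abstract's wording.
- For the sustained part of Hypothesis 2, state the benchmark proportion and report period-specific proportions against it.

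The cost is revised wording and slightly more analysis on data already being collected. The downside is wide intervals at late time-points and at small sites, so the benchmark comparison may be inconclusive there.
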